## Abstract

**Background:**

Children in Malawi face high rates of malnutrition and are at risk of not reaching their developmental potential. Community-based childcare centres (CBCCs) can be cost-effective platforms for scaling-up early childhood development (ECD) and nutrition social behaviour change (SBC) interventions. However, evidence also suggests potential synergies from coupling nutrition SBC with cash transfers (CT), given that rural households in Malawi face high levels of poverty and recurring extreme lean season food-security shocks. The Maziko trial is aimed at evaluating the effectiveness and cost-effectiveness of using CBCCs and parenting care groups as platforms to improve maternal diets and child nutrition and development by providing nutrition-sensitive SBC and CT intervention packages in communities already receiving a standard of care Government SBC program.

**Methods:**

We designed a 3-year cluster-randomised controlled trial in two districts of Malawi, including 156 communities randomised to one of four treatment arms: (1) standard of care (SoC) arm: receiving the standard Government SBC program; (2) SBC arm: receiving the SoC intervention with additional nutrition-sensitive SBC activities to improve nutritious food production, diets, and care practices for young children; (3) low CT arm: SoC plus SBC plus a maternal and child cash transfer ~ 17 USD per month; and (4) high CT arm: SoC plus SBC plus a maternal and child CT ~ 43 USD per month. The trial will enrol pregnant women and children < 2 years of age. The primary outcomes are maternal diet assessed using the mean probability of adequacy and child development assessed using the Malawi Developmental Assessment Tool. Intermediate outcomes along the programme impact pathways will also be measured, including maternal mental health, maternal empowerment, child feeding practices, and child nutritional status.

**Discussion:**

This is the first study to examine the impact and synergies of combining ECD SBC with nutrition-sensitive SBC and CTs on maternal and child outcomes during the first 1000 days. The findings from this evaluation will inform national ECD and nutrition programmes.

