## Methods

### Study objectives

The Maziko trial is aimed at evaluating the effectiveness and cost-effectiveness of using the integrated CBCC and parenting care-group platform to improve maternal and child nutrition and development by providing variations of nutrition-sensitive intervention packages in communities receiving standard Government support. The trial addresses one primary objective and several secondary objectives (Table 1).

**Table 1 Tab1:** Objectives of the Maziko trial

Primary objective
To determine the independent effect of nutrition social behaviour change (SBC) and combined effects of nutrition SBC integrated with one of two levels of cash transfers on the adequacy of nutrient intake in women 15–49 years of age at baseline who are pregnant or mothers of children 0–2 years of age at baseline, and on child development (motor, language, and cognition) in children (in utero to 2 years of age at baseline), over a 3-year implementation period
Secondary objectives

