#### Standard of care

The national Nutrition Policy and Strategic Plan, led by the Department of Nutrition and HIV/AIDs, Ministry of Health, and Ministry of Gender, Children, Disability and Social Welfare of Malawi focuses on care groups, run by mother leaders and volunteers to reach pregnant and breastfeeding women and children < 5 years of age with key nutrition services, including home visits, cooking demonstrations, and promotion of essential services. The standard of care (SoC) will ensure the establishment of care groups and training of mother leaders and volunteers, through a cascade training, using the government-approved modules and materials. There are five modules in total: (1) breastfeeding; (2) complementary feeding; (3) hygiene; (4) maternal health and nutrition; and (5) ECD. These materials were recently updated to integrate ECD concepts across all materials. The cascade training was rolled out from national to district to teaching authority (TA) to community level targeting health and nutrition actors, including District Nutrition Coordinating Committees, Area Nutrition Committees, Village Nutrition Committees, Health Surveillance Assistants, and Care Group Promoters and Cluster leads (mother volunteers).

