## Discussion

ECD programmes are considered among the most cost-effective investments in human capital [9], resulting in improvements in children’s cognitive, motor, and socio-emotional development [1, 8]. Nutrition-sensitive agricultural programmes, when well-implemented, can improve maternal and child dietary outcomes and, in some cases, children’s nutritional status [15, 16]. Further, CT programmes can improve food and nutrition intake, but have more inconsistent effects on micronutrient status and anthropometry [12, 13]. Combining these sectors may lead to substantial gains in effectiveness, efficiency, and cost. Existing evidence highlights the potential for additive and synergistic effects when combining ECD, nutrition, agriculture, and CT interventions [11, 16, 39, 40]. However, there is a need to rigorously assess these potential synergies. This article describes the rationale, design, and methods for the Maziko trial, a cRCT designed to evaluate the impact and cost-effectiveness of an integrated SBC ECD package coupled with nutrition-sensitive SBC and CT on the diets, nutrition, and development of young children and their mothers in rural Malawi. To our knowledge, this is the first study to examine the synergistic effects of combining ECD, nutrition, agriculture, and CT interventions on women’s and children’s diet, nutrition, and development outcomes.

The Maziko study will provide evidence on the effectiveness and cost-effectiveness of integrating ECD, nutrition, agriculture, and CT interventions to support households with young children in rural Malawi. The trial will inform the scaling-up of these services in Malawi. Results are likely to be generalisable to similar rural settings in sub-Saharan Africa with high poverty levels, where households face recurring extreme lean season shocks and constrained financial resources for child diets, nutrition, and development.

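### The Abstract and Discussion say the trial examines synergies between ECD, nutrition-sensitive SBC and cash, but its four arms cannot estimate any such interaction

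*Protocol article*

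**What the plan says.** The claim stands in two places. The Abstract, under Discussion, says: "This is the first study to examine the impact and synergies of combining ECD SBC with nutrition-sensitive SBC and CTs". The main Discussion says: "this is the first study to examine the synergistic effects of combining ECD, nutrition, agriculture, and CT interventions". Shortly before that sentence the main Discussion mentions additive and synergistic effects as separate possibilities and says the potential synergies need rigorous assessment.

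The arms are set out in the Abstract, under Methods, and again in Table 2 (Randomisation and masking), with 39 clusters each:

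- Arm 1: "standard of care (SoC) arm: receiving the standard Government SBC program"
- Arm 2: "SBC arm: receiving the SoC intervention with additional nutrition-sensitive SBC activities"
- Arm 3: "low CT arm: SoC plus SBC plus a maternal and child cash transfer"
- Arm 4: "high CT arm: SoC plus SBC plus a maternal and child CT"

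The Standard of care section lists five training modules, ending with "4) maternal health and nutrition; and (5) ECD", so core ECD content reaches all four arms. Under Nutrition-sensitive SBC interventions, the food security and livelihood, gender, adolescent and reinforced-ECD activities form one package. Table 2 gives that whole package to arms 2, 3 and 4.

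The primary objective (Table 1) asks for the independent effect of nutrition SBC and for the "combined effects of nutrition SBC integrated with one of two levels of cash transfers". It does not mention synergy.

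**The concern.** Because the main Discussion separates additive from synergistic effects, a reader will take synergy in its technical sense: the components together do more than the sum of what each does alone. The last paragraph of the Background points the same way, since it suggests that cash may make the behaviour change package more effective. Showing this needs the effect of cash in the absence of SBC, and for the wider claim the effects of the single sectors. No arm supplies either.

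What is at stake is the interpretation of the endline results, not an estimate or a test. If SBC plus cash does better than SBC alone, the text as written invites the label synergy for a difference that additive effects would also produce.

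**Working it through.** The document gives no figure for synergy, so there is none to reproduce. The check is whether the interaction is estimable from the arms.

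**Inputs.** Arm definitions from the Abstract (Methods) and Table 2; ECD content from Standard of care; the SBC package from Nutrition-sensitive SBC interventions.

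**Step 1: SBC by cash.** Let S be the effect of the SBC package, L and H the effects of low and high cash without SBC, and SL and SH the interactions. With μ the standard-of-care mean, the arm means are:

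| Arm | Mean |
|---|---|
| 1. Standard of care | μ |
| 2. SBC | μ + S |
| 3. SBC + low cash | μ + S + L + SL |
| 4. SBC + high cash | μ + S + H + SH |

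There are six parameters (μ, S, L, H, SL, SH) and four means. The design matrix has rank 4.

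- Arm 2 − arm 1 = S: estimable.
- Arm 3 − arm 2 = L + SL: estimable only as a sum.
- Arm 4 − arm 2 = H + SH: estimable only as a sum.
- L, H, SL and SH separately: not estimable.
- Arm 4 − arm 3 = (H − L) + (SH − SL): the difference between cash levels in the presence of SBC, which is not an interaction with SBC.

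**Step 2: what this means in numbers.** The values here are assumed for illustration and are not from the document. Suppose SBC gains 0.20 SD and SBC plus cash gains 0.50 SD, both against standard of care. The increment of cash over SBC is 0.50 − 0.20 = 0.30 SD. The interaction is 0.30 minus the unobserved effect of cash alone:

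| Cash alone (SD) | Interaction (SD) | Reading |
|---|---|---|
| 0 | 0.30 − 0 = +0.30 | synergy |
| 0.30 | 0.30 − 0.30 = 0 | additive |
| 0.40 | 0.30 − 0.40 = −0.10 | antagonism |

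The same trial result fits all three rows. That does not make the three equally plausible; it means the randomised data cannot choose between them.

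**Step 3: the sectors.** Core ECD content is constant across the arms, so neither its effect nor its interaction with anything else is estimable. The four added SBC components always occur together. Four components have 2^4 − 1 = 15 main effects and interactions among them, and arm 2 − arm 1 gives only their sum.

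**Step 4: what would have been needed.** Adding a low-cash-only arm makes SL estimable but not SH. Adding low-cash-only and high-cash-only arms raises the rank to 6 of 6. Trial status reports that recruitment was completed on 11 July 2022, so this only shows what is missing.

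**The case against.** The strongest reply is that nothing in the plan targets synergy. The word is absent from the primary objective, the eleven secondary objectives, the sample size section and the statistical analysis. The arms identify both quantities that the primary objective names. This stands. A reader might infer that the primary objective is unsupported or that the choice of arms is wrong for it; the documents do not bear that out.

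A reader might also infer that the increment of cash over SBC has been left out of the analysis. The Statistical analysis section plans comparisons between randomised arms with a dummy variable for each intervention, and that model yields each cash arm against SBC and high against low cash. A full list of contrasts commonly sits in an analysis plan, which is not shown here, so its absence is no fault.

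A third tempting inference is that the trial will mislead a policy choice between cash alone and cash plus SBC. The documents do not pose that choice. They ask what to add to the Government programme, and the economic evaluation compares the interventions with standard of care. Nor does any passage say that a difference between SBC plus cash and SBC will be read as an interaction.

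Finally, synergy is sometimes used loosely here, as in Programme impact pathways, and the planned mediation and process analyses give the verb examine some content. This stands only in part. Those analyses do not yield a randomised estimate of the interaction, and the main Discussion uses the word in its strict sense when it sets synergistic beside additive and calls for rigorous assessment.

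**Conclusion.** The two synergy statements, in the Abstract and the main Discussion, claim something that the design cannot deliver. Neither SBC-by-cash interaction is estimable (rank 4 for six parameters), and no contrast separates ECD, nutrition and agriculture from one another. The conclusion rests only on the arm definitions and on reading synergy as departure from additivity. It does not depend on sample size, intracluster correlation or covariate adjustment, and no analysis plan could change it with these arms.

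The fault is limited to these claims. The trial can validly estimate SBC against standard of care, each package against standard of care, the increment of each cash level over SBC, and high against low cash. No primary estimate, test or sample size is affected.

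**What to change.** In both the Abstract (Discussion) and the main Discussion, replace the synergy claims with wording such as: the effect of nutrition-sensitive SBC added to the standard of care, and the incremental effect of cash, at two levels, added to SBC. Add one sentence stating that no SBC-by-cash interaction, between-sector synergy or cash-alone conclusion will be drawn from the randomised comparisons. The detailed list of contrasts can be left to the statistical analysis plan.

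The cost is a few lines of text. Arms, conduct, data collection and planned models stay as they are.

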**Trial registration:**

ISRCTN ISRCTN53055824. Registered on 7 March 2022.

**Supplementary Information:**

The online version contains supplementary material available at 10.1186/s13063-023-07782-3.

## Background

Over 250 million children are at risk of not reaching their developmental potential because of poverty, malnutrition, and other related adversities [1]. Estimates of the global burden of malnutrition indicate that undernutrition causes over 3 million child deaths per year [2] and that 155 million children aged < 5 years are stunted [3]. Micronutrient deficiencies contribute to both maternal and child mortality risks and affect children’s physical and mental development [4]. Malawi has one of the highest rates of chronic malnutrition in the world, with 37% of children aged 6–59 months being moderately or severely stunted [5]. Thirty-three percent of women and 63% of children < 5 years of age in Malawi are anaemic [5].

Early childhood development (ECD) involves interlinked physical, cognitive, and socio-emotional processes [6, 7]. Interventions designed to improve ECD have been shown to improve children’s cognitive, motor, and socio-emotional development [1, 8] and are considered among the most cost-effective investments in human capital [9]. Despite evidence on the effectiveness of ECD programmes, coverage and quality of implementation in low- and middle-income countries are low [1, 6]. In practice, ECD programmes are implemented through health, nutrition, education, and social protection sectors [10] and are most effective when targeting younger and more disadvantaged children and when also providing integrated health and nutrition services [6, 11]. Effective approaches also involve improving the quality of the learning environment and providing services to children directly. Training parents and involving them in practice and skill-building sessions are more effective than providing information alone [1].

Systematic reviews of the effects of cash transfers (CT) on maternal and child nutrition outcomes generally find consistent positive effects on food and nutrition intake and less consistent evidence suggesting small or null effects on micronutrient status and anthropometric outcomes, largely due to heterogenous programme designs [12, 13]. Evidence from CT programmes in Malawi includes an evaluation of the Social Cash Transfer Programme (SCTP), an unconditional CT programme targeted to ultra-poor, labour-constrained households, reaching all rural districts, with transfers ranging from 3 to 7 USD/month (2600–5600 MWK) depending on household size.^1^ A randomised controlled trial (RCT) of the SCTP found positive effects on household food consumption including increases in meal frequency, caloric availability, and reduction in the hunger gap but no impact on child anthropometry [14]. However, the SCTP is not been explicitly designed to address the multiple drivers of malnutrition and transfer levels remain low relative to the cost of living and are not indexed to inflation.

Evidence also suggests that well-implemented, nutrition-sensitive agricultural interventions have the potential to make important contributions to improving maternal and child nutrition outcomes [15, 16]. Findings from rigorous studies point to generally consistent impacts on dietary outcomes but less consistent impacts on children’s nutritional status, with scant evidence for other population groups. In Malawi, the NEEP-IE trial, an IFPRI/Save the Children RCT, compared the Government standard of care (SoC) behaviour change communication (BCC) package (including BCC on ECD, nutrition, and health) to SoC plus a more intensive nutrition-sensitive agriculture BCC package. The SoC package was equivalent to the treatment that was found to be most effective in a World Bank Protecting Early Childhood Development (PECD) four-arm trial [17]. The NEEP-IE trial showed that the nutrition-sensitive agricultural intervention implemented through community-based childcare centres (CBCCs) and parenting/care groups had large, positive effects on diets in pre-schoolers 3–6 years old and younger siblings 6–24 months old and on linear growth and stunting prevalence in younger siblings 6–24 months old [18]. A survey conducted 1 year post-trial showed that some benefits persisted (from improved nutrition to improved child development) whilst most other effects faded out. An economic evaluation found that the NEEP-IE programme had benefit–cost ratios from 3.6 to 24.7 [19]. Partially driven by the NEEP-IE trial findings, the Government of Malawi, through a grant from the World Bank, is in the process of scaling up components of the NEEP-IE package through the Investing in Early Years Program (IEYP) across 13 districts in the country [20].

The evidence from Malawi thus suggests that linking CBCCs and care groups can be a cost-effective platform for scaling up nutrition interventions. However, the literature also suggests potential synergies from coupling nutrition-sensitive BCC packages and CT [21]. Literature from Malawi also highlights that, in addition to high poverty levels, households also face recurring extreme lean season shocks when financial resources are typically most constrained. Theory would suggest that relaxing household budget constraints through unconditional CT may reduce vulnerability to price shocks, making the BCC package more effective. The scale-up of the IEYP in Malawi provides an ideal opportunity to support the roll-out and test the cost-effectiveness of additional, alternative approaches to improve infant and maternal nutrition. The Maziko study is a cluster-RCT (cRCT) designed to evaluate the impact and cost-effectiveness of an integrated SBC ECD package coupled with nutrition-sensitive BCC and CT on the diets, nutrition, and development of young children and their mothers in rural Malawi. This article describes the rationale, design, and methods for the Maziko trial.

## Methods

### Study objectives

The Maziko trial is aimed at evaluating the effectiveness and cost-effectiveness of using the integrated CBCC and parenting care-group platform to improve maternal and child nutrition and development by providing variations of nutrition-sensitive intervention packages in communities receiving standard Government support. The trial addresses one primary objective and several secondary objectives (Table 1).

**Table 1 Tab1:** Objectives of the Maziko trial

Primary objective
To determine the independent effect of nutrition social behaviour change (SBC) and combined effects of nutrition SBC integrated with one of two levels of cash transfers on the adequacy of nutrient intake in women 15–49 years of age at baseline who are pregnant or mothers of children 0–2 years of age at baseline, and on child development (motor, language, and cognition) in children (in utero to 2 years of age at baseline), over a 3-year implementation period
Secondary objectives
1. To examine the effects of the randomised interventions on the Global Diet Quality Score in women 15–49 years of age at baseline who are pregnant or mothers of children 0–2 years of age 2. To examine the effects of the randomised interventions on the adequacy of nutrient intake in children in utero to 2 years of age at baseline 3. To examine the effects of the randomised interventions on height, height-for-age Z-score (HAZ), stunting (HAZ < − 2), weight, weigh-for-height Z-score (WHZ), wasting (WHZ < − 2), mid-upper arm circumference (MUAC), and head circumference in children in utero to 2 years of age at baseline 4. To examine the differential effects of the randomised interventions in the following pre-specified subgroups: a. Female and male children b. Intervention exposure timing/duration (pre-natal/post-natal) c. Subgroups formed by categorising household wealth, food security status, and maternal empowerment 5. To examine effects along the programme impact pathways (PIPs) linking programme implementation of each randomised intervention to nutrient adequacy of intake in women 15–49 years of age at baseline who are pregnant or mothers of children 0–2 years of age and children in utero to 2 years of age at baseline, and other outcomes by assessing: a. Fidelity of intervention implementation for each of the randomised interventions, defined as conformance with implementation specifications b. Quality of community-based childcare centres (CBCC) and care group training and supervision c. CBCC and care group volunteer capacity and service provision as related to the “All Children Surviving and Thriving” framework as assessed by questionnaire and observations d. Attained maternal knowledge and practices as related to the “All Children Surviving and Thriving” framework as assessed by questionnaire and observations 6. To examine the differential effects of the randomised interventions on women’s empowerment and maternal depressive symptoms, and how changes in these indicators mediate the effects on child-level nutrition and developmental outcomes 7. To examine the differential effects of the randomised interventions on household expenditure levels, shares of expenditures, poverty, and food-insecurity levels 8. To examine the differential effects of the randomised interventions on household food consumption elasticities for calories and micronutrients, what factors affect the consumption elasticities, and how changes in elasticities mediate the effects on child-level outcomes 9. To examine the differential effects of the randomised interventions on pregnant women and mothers of young infants’ willingness to pay (WTP) for nutrient-dense complementary foods, what factors affect the WTP for nutrient-dense complementary foods, and how changes in WTP mediate the effects on child-level outcomes 10. To assess costs and incremental cost-effectiveness of the randomised interventions compared to the standard of care 11. To examine the effects of the randomised interventions on haemoglobin concentration and anaemia prevalence in women 15–49 years of age at baseline who are pregnant or mothers of children 0–2 years of age and children in utero to 2 years of age at baseline (conditional on additional funding for data collection)

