### Sample size and power

The primary outcomes of the trial include women’s diet assessed using the mean probability of adequacy (MPA) of micronutrient intake and child development (motor, language, and cognitive) assessed using the Malawi Developmental Assessment Tool (MDAT). Power calculations based on available clusters in targeted districts and resource availability suggested ~ 40 clusters per intervention arm and 20 households (mother–child pairs) per cluster. Calculations based on MPA and a cRCT design (inter-cluster correlation coefficient (ICC) = 0.05) suggested a Minimum Detectable Effect Size (MDES) of 0.31 SDs. For reference, the effect of the nutrition SBC intervention found during NEEP-IE trial on MPA of children 3–6 years old was 0.34 SDs [27]. Similar calculations for MDAT *Z*-score suggested an MDES of 0.26 SDs (ICC = 0.02). The effect of the SBC intervention on children 6–24 months of age found after a 2-year period (with only 1 year with intervention) during the NEEP-IE trial was 0.23 SDs.

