### Randomisation and masking

Clusters were randomly assigned to one of four intervention arms using a restricted randomisation procedure [28]. Restricted randomisation involves modelling selection using a set of village-level variables to ensure balance across the intervention arms. The variables in the restricted randomisation were selected based on their potential influence on the main study outcomes and their potential influence on participation in the interventions [28]. The village-level variables included in the model were population size, total per capita household expenditure, household dwelling state, household drinking water source, women’s empowerment, maternal caloric intake, maternal micronutrient intake, maternal age, pregnancy status, maternal weight, maternal education, maternal marital status, child age, child sex, child weight, child height, and child and total MDAT score. Household-level data were used to generate village-level aggregates for all variables except for population size which was available at the village level. We developed a programme using Stata 17 [29] to randomly allocate clusters to four different arms stratifying by district. The randomisation was stratified by district to allow for the same approximate number of clusters within each of the intervention arms in each of the two districts. The algorithm then regressed selection into the intervention arm on the village-level variables. The algorithm tested 5000 random allocations and then selected the permutation that minimised the *R*^2^ for the predicted selection. Description of the intervention arms is provided in Table 2.

**Table 2 Tab2:** Description of the four intervention arms

Intervention arm	Care group component	SBC component	Cash transfer component	Number of clusters
Standard of care (SoC)	Yes	No	No	39
Nutrition-sensitive social and behaviour change (SBC)	Yes	Nutrition-sensitive SBC on agriculture, gender, adolescence, and extra ECD	No	39
SBC + low cash	Yes	Nutrition-sensitive SBC on agriculture, gender, adolescence, and extra ECD	~ $17 per month	39
SBC + high cash	Yes	Nutrition-sensitive SBC on agriculture, gender, adolescence, and extra ECD	~ $43 per month	39

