	**Data collection round**		
**Data collected**	**Baseline**	**Mid-line (1.5 years)**	**Endline (3 years)**
*CBCC/village level*			
Village infrastructure and development projects	I		I
CBCC infrastructure and staff	I		I
Parenting/care groups	I		I
Market prices	I	I	I
*Household level*			
Demographics, socioeconomic status	I		I
Expenditures	I	I	I
Agriculture production	I	I	I
*Maternal level*			
Programme exposure	I	I	I
Women's empowerment (Pro-WEAI)		IDI/FGDs	
Role in household decision-making around production and income	I	I	I
Access to productive capital	I	I	I
Access to financial services	I		I
Time allocation	I		I
Group membership	I		I
Physical mobility	I		I
Intrahousehold relationships	I		I
Autonomy in decision-making	I		I
New general self-efficacy scale	I		I
Life satisfaction			
Attitudes about domestic violence	I		I
Maternal depressive symptoms (SRQ)	I	I	I
Height and weight	M	I	M
Haemoglobin (conditional on additional funding)			B
24-h dietary recall	I	I	I
IYCF knowledge and practices	I	I	I
Willingness to pay for specialised foods	I	I	I
*Paternal level*			
Women’s empowerment (Pro-WEAI)	I	IDI/FGDs	I
*Child level*			
Birth information (date, time, mode, place, complications, care, weight)	R	R	
Immunisation and vitamin A	I	I	I
7-day morbidity symptoms, health record (clinic visits, hospitalisations)	I	I	I
Height and weight	M	I	M
Child development (MDAT)	I/O		I/O
Family care indicators	I	I	I
24-h dietary recall			I

*Abbreviations: B*, blood; *CBCC*, community-based childcare centre; *FGD*, focus group discussion; *I*, interview; *IDI*, in-depth interview; *IYCF*, infant and young child feeding; *M*, measurement; *MDAT*, Malawi Development Assessment Tool; *O*, observation; *SRQ*, self-reported questionnaire; *T*, test; *WEAI*, women empowerment in agriculture index

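### Secondary objective 4c tests effect modification by wealth, food security and empowerment through categories only, which loses about 36% of the interaction information with a median split and about 21% with tertiles if the gradient is roughly linear

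*Protocol article*

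**What the plan says.** Objective 4 in Table 1 (Study objectives) reads: "To examine the differential effects of the randomised interventions in the following pre-specified subgroups". Items 4a (child sex) and 4b (pre-natal or post-natal exposure) are categorical by nature and are not in question. Item 4c is "Subgroups formed by categorising household wealth, food security status, and maternal empowerment". The article gives no number of categories and no cut-points for 4c. The Statistical analysis section describes no interaction model and no analysis with a continuous modifier.

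On the data available:

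- **Wealth.** The balancing variables under Randomisation and masking include "total per capita household expenditure, household dwelling state, household drinking water source". That section says the village values were aggregated from household-level data. Table 3 schedules expenditures at baseline, and also "Demographics, socioeconomic status". No wealth index is defined.
- **Empowerment.** The same list includes "women’s empowerment, maternal caloric intake, maternal micronutrient intake", and Table 3 schedules many empowerment components at baseline. The form of the individual score is not stated.
- **Food security.** Objective 7 names "household expenditure levels, shares of expenditures, poverty, and food-insecurity levels" as outcomes. Table 3 has no food-security row, and no instrument or scale is given.

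**The concern.** Cutting a graded score into bands treats households just either side of a cut as different and households within a band as alike. If the treatment effect changes gradually along the score, that discards information, and the result also depends on where the cut falls.

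Interaction tests are already weak compared with tests of main effects, and the article's power figures cover main effects on the two primary outcomes only. The Background argues that relaxing the household budget constraint may make the behaviour-change package more effective. A gradient in household resources is therefore a natural thing for this trial to look for, and an avoidable loss of power there is worth removing.

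**Working it through.** **Plan's own figure.** There is none for this point. The only power statements are the detectable effects for the primary outcomes (for dietary adequacy, the article "suggested a Minimum Detectable Effect Size (MDES) of 0.31 SDs"; for the development score, 0.26 SD). They do not enter the calculation below.

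**Inputs from the article.** 39 clusters per arm (Table 2); 20 households per cluster (planning statement: "40 clusters per intervention arm and 20 households"); ICC 0.05 for the dietary outcome.

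**Assumptions, not in the article.** A normally distributed modifier, an interaction linear in it, two-sided 5% tests, and a slope difference chosen so that the continuous test has about 80% power.

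**Step 1: information kept.** For a standard normal score, the share kept by grouping is the between-group share of its variance. For two groups with a proportion p above the cut c, this is φ(c)² / [p(1 − p)].

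- Median split: φ(0)² / 0.25 = (1/2π) / 0.25 = 2/π = 0.637, a loss of 36.3%.
- 80/20 split: c = 0.842, φ(c) = 0.280, so 0.0784 / 0.16 = 0.490, a loss of 51.0%.

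For k groups it is Σ pⱼ × (group mean)². For tertiles the outer means are ±0.3636 / (1/3) = ±1.091, giving (2/3) × 1.091² = 0.793, a loss of 20.7%.

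| Grouping | Information lost |
|---|---|
| Quintiles | 10% to 11% |
| Quartiles | 14% |
| Tertiles | 20.7% |
| Median split | 36.3% |
| 60/40 | 37.8% |
| 70/30 | 42.4% |
| 80/20 | 51.0% |
| 90/10 | 65.8% |

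**Step 2: power.** If the continuous test has 80% power, the grouped test has Φ[(1.960 + 0.842) × √(share kept) − 1.960].

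- Median split: 2.802 × √0.637 − 1.960 = 0.276, power 61%.
- Tertiles with a trend score: 2.802 × √0.793 − 1.960 = 0.535, power 70%.
- 80/20 split: 2.802 × √0.490 − 1.960 = 0.001, power 50%.

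**Step 3: simulation check.** One two-arm comparison, 39 against 39 clusters of 20, ICC 0.05, slope difference 2.8016 / √(780/2) = 0.142 SD per SD of the modifier, 3,000 runs.

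| Test | Power, modifier not clustered | Power, 10% of modifier variance between clusters |
|---|---|---|
| Continuous | 0.81 | 0.79 |
| Tertile trend | 0.72 | 0.69 |
| Median split | 0.63 | 0.59 |
| Tertiles, 2 df | 0.61 | 0.59 |
| 80/20 split | 0.51 | 0.47 |

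With no true interaction, rejection rates were 0.045 to 0.065 (2,000 runs).

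**Step 4: the reverse case.** If the true modification is a step at the median, the linear-score test keeps 2/π, about 64%, of the information that the split uses. The advantage then reverses.

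**Step 5: scale.** The Cash transfers section gives rural per capita consumption as mean MWK 185,418 and median MWK 151,157, so it is right-skewed. If it is lognormal, σ² = 2 ln(185,418 / 151,157) = 0.409 and σ = 0.64. If the interaction is linear in log consumption, a linear test on the raw scale keeps σ² / (exp(σ²) − 1) = 0.409 / 0.505 = 0.81. That is hardly better than tertiles (0.79), so the scale has to be chosen in advance.

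**The case against.** The strongest reply is that one line in an objectives table is not an analysis model. The article is condensed, its analysis plan is not shown, and cut-points and interaction models commonly sit there. This stands in part. The missing cut-points are no fault, and a reader might infer that they are still open to choice; the article calls these subgroups pre-specified, so they may be fixed elsewhere. But forming the subgroups by categorising is stated, and an analysis plan that follows the objective inherits it.

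Second, linearity is an assumption. Thresholds are plausible here, since the transfer values are motivated partly by a poverty line and a diet-affordability gap. This stands: under a step at the cut, categories lose nothing and the linear test is the weaker one.

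Third, a reader might infer that continuous scores exist for all three modifiers. The article supports this for expenditure and makes it plausible for empowerment, but does not show it for food security.

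Fourth, a reader might infer that these analyses will decide who should receive cash. The article says only that the findings will inform national programmes and scale-up.

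**Conclusion.** The point holds as a limited criticism of a stated method. For a graded modifier that is roughly normal, with a roughly linear gradient, categorising costs about 36% of the interaction information with a median split, about 21% with tertiles and about 11% with quintiles. It is tempting to read 36% as the most that can be lost. It is the smallest loss from any two-group cut of a normal score; unequal cuts lose more. The article does not say which grouping applies, so no single figure can be attributed to this plan.

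The power figures illustrate the size of the effect. They rest on an assumed slope and modifier distribution, with only the cluster numbers and ICC taken from the article. The point concerns one part of one secondary objective and leaves the primary analyses untouched.

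**What to change.** Reword objective 4c and carry the wording into the analysis plan. Where a continuous or graded baseline measure exists, the pre-specified test of differential effect is the interaction of arm with that baseline score, in the same multilevel model.

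- State the measure and its scale in advance: log per capita expenditure or a defined wealth score, and the empowerment score.
- Include food security only if a graded scale was collected at baseline; otherwise keep its categories and give the definition.
- Add a spline term as a check for non-linearity.
- Keep categories, such as tertiles, to display the estimates.

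The change needs wording and slightly more analysis, with no new data. It should be recorded before the endline results are unblinded. Its downside is that the linear interaction assumes an approximately straight gradient and has less power than the split if the true modification is a step at the chosen cut.
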